## Abstract

**Background.:**

Development disorders and delays are recognised as a public health priority and included in the WHO mental health gap action programme (mhGAP). Parents Skills Training (PST) is recommended as a key intervention for such conditions under the WHO mhGAP intervention guide. However, sustainable and scalable delivery of such evidence based interventions remains a challenge. This study aims to evaluate the effectiveness and scaled-up implementation of locally adapted WHO PST programme delivered by family volunteers in rural Pakistan.

**Methods.:**

The study is a two arm single-blind effectiveness implementation-hybrid cluster randomised controlled trial. WHO PST programme will be delivered by ‘family volunteers’ to the caregivers of children with developmental disorders and delays in community-based settings. The intervention consists of the WHO PST along with the WHO mhGAP intervention for developmental disorders adapted for delivery using the android application on a tablet device. A total of 540 parent-child dyads will be recruited from 30 clusters. The primary outcome is child's functioning, measured by WHO Disability Assessment Schedule – child version (WHODAS-Child) at 6 months post intervention. Secondary outcomes include children's social communication and joint engagement with their caregiver, social emotional well-being, parental health related quality of life, family empowerment and stigmatizing experiences. Mixed method will be used to collect data on implementation outcomes. Trial has been retrospectively registered at ClinicalTrials.gov (NCT02792894).

**Discussion.:**

This study addresses implementation challenges in the real world by incorporating evidence-based intervention strategies with social, technological and business innovations. If proven effective, the study will contribute to scaled-up implementation of evidence-based packages for public mental health in low resource settings.

**Trial registration.:**

Registered with ClinicalTrials.gov as Family Networks (FaNs) for Children with Developmental Disorders and Delays. Identifier: NCT02792894 Registered on 6 July 2016.

## Background

Developmental disorders are lifelong conditions that are characterised by early childhood onset and delay in central nervous system development and maturation. This includes conditions such as autism spectrum disorder and intellectual disabilities (World Health Organization, 1992). Developmental disorders and delays are a public health priority and are included in the World Health Organisation mental health Gap programme (WHO mhGAP) to bridge the treatment gap for priority mental health conditions in low resource settings (Dua *et al*. 2011). WHO mhGAP guidelines recommend Parents Skills Training (PST) for developmental disorders and delays.

Based upon the findings of a systematic review and meta-analysis of literature WHO has developed a PST programme for children with developmental disorders and delays (Reichow *et al*. 2013). Two key features of WHO PST are (a) the programme takes a task-shifting approach where non-specialists including social workers, nurses, teachers, community volunteers, caregivers and parents can deliver this programme in community-based facilities or schools to the families of children with developmental disorders and delays (b) it takes a trans-diagnostic approach – it addresses a range of different developmental disorders and conditions and does not require an expert diagnosis of developmental disorders and delays to qualify treatment. However fragile health systems, lack of funding and lack of trained health personnel remain the key bottlenecks to scale up and sustainability of such priority public health intervention packages in low resource settings (Eaton *et al*. 2011).

To overcome these challenges, we developed an integrated model of service delivery (incorporating social, technological and business innovations (Fig. 1) for children with developmental disorders and delays in low resource settings (Hamdani *et al*. 2015). An android application was developed to incorporate the WHO mhGAP-IG diagnostic and management guidelines and WHO PST for developmental disorders and delays in a standardised way. The intuitive tablet-based training and intervention delivery tool can be used to deliver evidence-based interventions in low resource settings by non-specialist. The model was found to be feasible, acceptable and resulted in change in client outcomes. The proof of concept of the integrated model of service delivery has already been published (Hamdani *et al*. 2015).

**Fig. 1. fig01:**
[figure not shown]
Integrated model of service delivery.

### Objectives and hypothesis

The objectives of this study are to evaluate at scale the effectiveness and implementation of WHO PST programme for children with developmental disorders and delays in rural Pakistan.

To obtain the objectives of the study, following research questions are formulated; (1) Can the WHO PST delivered by family volunteers improve functioning in children with development disorders and delays in rural Pakistan? (2) Can the WHO PST programme improve child's social communication and joint engagement with caregivers, improve child's social and emotional well-being, improve family empowerment, and result in better caregiver's health related quality of life? (3) Can the integrated model of service delivery for developmental disorders and delays (Hamdani *et al*. 2015) serve as a scalable method of delivering WHO PST programme in low resource settings? (4) What factors can inhibit and promote the large-scale implementation of WHO PST programme for developmental disorders and delays?

The primary effectiveness hypothesis is that WHO PST programme for children with developmental disorders and delays plus Enhanced Treatment as Usual (ETAU) is superior to ETAU alone in improving functioning in children with developmental disorders and delays in rural Rawalpindi.

Secondary effectiveness hypotheses are that WHO PST programme for children with developmental disorders and delays is associated with improvements in child's social communication and joint engagement with the caregiver, Child's social and emotional well-being, family empowerment, care giver's health related quality of life and reduction in family's stigmatizing experiences.

Primary implementation hypothesis is that the integrated model of service delivery for WHO PST program is a feasible, acceptable, appropriate implementation strategy that results in fidelity, adoption and penetration of the parents’ skills training program and increases the reach of evidence-based services for families and children with development disorders and delays in low resource settings.

## Methods

### Study settings

Study will be conducted in 30 rural Union Councils (UCs)-the smallest administrative units- of sub-district Gujar Khan in Rawalpindi district, Pakistan (approximate population 1 million). Sub-district Gujar Khan, representative of northern Punjab and Pothohar region, is a rural sub-district situated about 35 km south east of the Rawalpindi city.

Each UC has a Basic Health Unit (BHU) that provides health care to local population. BHU is staffed by a medical doctor, a dispenser, 15–20 Lady Health Workers (LHWs) working under supervision of Lady Health Supervisor, Lady Health Visitor, and a Vaccinator. Nearest specialist mental health care facility is the Institute of Psychiatry, Rawalpindi. One public special education school for children with special needs caters to the needs of children with all kinds of special needs in Gujar Khan.

### Design

The trial is defined as an effectiveness implementation hybrid cluster randomised trial-type II because the focus of evaluation is the effectiveness of intervention delivery and implementation strategies at scale. This is the appropriate design to use because there is evidence to support the feasibility, fidelity, acceptability, appropriateness of the implementation strategies in the proposed settings (Hamdani *et al*. 2014, 2015). There is evidence on the effectiveness of WHO PST program strategies (Reichow *et al*. 2013; Rahman *et al*. 2016*a*). However, there is no evidence on the effectiveness of intervention and implementation strategies at scale. This will be the first study to evaluate the effectiveness of scaled up implementation of WHO PST program in real world settings.

The first and second research questions will be answered by single blind cluster randomised control trial (cRCT) with two arms. Implementation effectiveness will be evaluated using the updated implementation research framework of Proctors *et al*. (2011) and the RE-AIM framework (http://re-aim.org/). We will use the Applied Mental Health Research Dissemination and Implementation (AMHR D&I) measurements to collect data at organization, provider and consumer levels post program implementation (AMHRG, personal communication). We will calculate the RE-AIM basic and summary indices on implementation outcomes. Quantitative and qualitative techniques will be utilised to supplement the implementation data. Data will be gathered from the implementation checklists (number of family volunteer trained, number of Family Networks established, tracking attendance of sessions and implementation and intervention fidelity) completed during the trial and through process evaluation during and after intervention delivery.

A cRCT design having UC as the unit of randomisation was preferred. Randomising smaller units, for example villages within the UCs, would lead to contamination and spillage of information in between the intervention and control villages. Hence, randomising a UC could reduce the probability of contamination between the two groups.

## Interventions

### WHO PST programme delivered by family volunteers

The core of the intervention is the WHO PST programme delivered within the broader context of WHO mhGAP programme implementation in Pakistan. WHO PST programme for children with developmental disorders and delays (field trial version 1.0) consists of eight sessions delivered in group format by a lay-facilitator. The PST Programme aims to provide evidence-based PST for caregivers of children with developmental disorders and delays that can be implemented locally in low- and middle-income countries. The primary aims of the programme are to promote better understanding and acceptance of developmental disorders and developmental delays and help parents apply skills that promote child development, communication and functioning. The secondary aims of the programme include strengthening caregivers’ coping skills and psychological well-being, and promoting child adaptive behaviours. It is expected that the programme will facilitate stigma reduction against persons with developmental disorders and result in increased inclusion and participation of children with developmental disorders and delays. The WHO PST programme is available on request.

Following the WHO PST adaptation guide, we adapted the pre-publication draft of the WHO PST programme for children with developmental disorders and delays for implementation in rural Rawalpindi, Pakistan. The adapted WHO PST programme for children with developmental disorder and delays delivered by family volunteers *consists* of nine weekly sessions. It is delivered by a ‘champion’ family volunteer in group settings through the use of intuitive tablet-based android application that serves as a training, intervention-delivery and monitoring tool. The key psycho-educational contents (‘key messages’ and strategies) of PST have been incorporated into ‘real-life’ narratives of the lives of three children with developmental disorders, their family members, and other supporting characters. An artist has converted the characters into ‘Avatars’ (graphic image representing each character) (Fig. 2), which are used to voice the narrative scripts. The details of the service delivery model and training, supervision and monitoring tool have been described elsewhere (Hamdani *et al*. 2015).

**Fig. 2. fig02:**
[figure not shown]
Avatar-Assisted Cascade Training (ACT).

Providers of PST programme for children with developmental disorders and delays are ‘champion’ family volunteers. These are parents or caregivers of children with developmental disorders and delays, have at least eight grades of formal education, are voluntarily willing to be trained and supervised by the trainers for at-least 6 months duration of the programme and cascade the training to 4–5 families in their villages. Our earlier work has established that lay health workers can deliver evidence-based psychological interventions in Pakistan (Rahman *et al*. 2008, 2016*b*). The training and supervision of champion family volunteers will follow a cascade model (Murray *et al*. 2011). The training in the WHO PST will be delivered using an android application hosted on a tablet device. The master trainers will train 10 trainers in the WHO PST programme. The training will consist of 10 days class-room training followed by case studies under the supervision of master trainer. The master trainer will perform live competency rating of the trainers on the case studies using an adapted version of ENhancing Assessment of Common Therapeutic factors (ENACT) for PST for developmental disorders and delays (Kohrt *et al*. 2015). The trainers have all completed at-least Masters in Clinical Psychology and have at-least 1 year of experience in working with children and families with developmental disorders and delays.

Only competent trainers (having mean score of 2.5 on each domain of ENACT adapted for WHO PST programme competency and fidelity rating) will be allowed to train and supervise champion family volunteers. The trainers will cascade down the training to the champion family volunteers using tablet-based tool, who will, then, deliver the PST programme to the 4–5 families under their care in local villages.

The champion family volunteers will be supervised by the trainers, who will be supervised by the master trainers on monthly basis. The fidelity of program delivery will be established by the master trainers by rating a random sample of sessions using the ENACT adapted for WHO PST program.

### Enhanced treatment as usual

Treatment as usual in primary healthcare centres in Rawalpindi for childhood developmental disorders usually consists of no treatment, or a range of alternate treatment regimes, such as multi-vitamin syrups and tablets. Evidence-based mental health care is currently not available in primary healthcare centres. For this study, the treatment as usual is enhanced in two ways:(a) LHWs in the ETAU arm will receive training in recognising signs and symptoms of developmental disorders and delays and making referrals to their primary care physicians for treatment; and (b) These primary care physicians will receive training in mhGAP developmental disorders standard module by the specialist at Institute of Psychiatry, WHO Collaborating Center for mental health in Pakistan.

If, during this treatment or during the study's assessments participants in ETAU arm show severe psychiatric disorders (e.g. psychosis, uncontrolled epilepsy) or problems (e.g. behavioural problem) that require immediate specialist treatment and follow-up, they will be referred to the child mental health facility at the Institute of Psychiatry, WHO Collaborating Center. The ETAU group will receive treatment when both arms will complete their follow up evaluation.

### Participants’ recruitment

#### Inclusion criteria

Children aged between 2 and 12 years residing in the study area for the duration of the study will be invited to participate in the trial. Inclusion criteria are as follows:
Children who are screen positive on any of the Ten Questions Screen questionnaire items # 1,4,5,7,8,9,10 for neurodevelopmental delay (Durkin *et al*. 1995)Diagnosed as developmental disorder/delays according to clinical assessment (History & clinical examination for developmental delay in motor, communication, social, cognitive, daily living skills domains according to mhGAP developmental disorders guidelines for clinical assessment in primary healthcare settings.

#### Exclusion criteria

The exclusion criteria are;
Co-morbid physical or mental conditions in the child requiring inpatient hospitalisationDeafness or blindness in the child or caregiver.Primary caregiver not available or unwilling to participate in the intervention programme for 6 monthsPhysical or mental conditions in the primary caregiver needing inpatient hospitalisation or frequent outpatient visits (more than two times a month).All these conditions will be observed by the trained assessor and will be inquired from the care-givers and family members using a checklist.

### Procedure to identify eligible participants

Prior to randomisation, key stakeholders (village elders and the primary health care staff) will be informed about the study procedures and their permission will be sought. HDRF has a database of about 3000 families and children with developmental disorders and delays gathered by interactive voice response (Hamdani *et al*. 2015) and snowballing sample technique as a part of the Foundation's service delivery to the community.

For the purpose of the trial we will need to identify 540 parent-child dyads from within 30 clusters (18 parent-child dyads from each cluster) to complete baseline and endpoint assessments. However according to the existing database of children, we expect that in each UC/cluster there will be more than 18 children fulfilling the eligibility criteria. For the purpose of the trial, within each UC, evaluation zones will be made to assess the impact of PST programme for children with developmental disorders and delays delivered by family volunteers.

These evaluation zones will be made by randomly selecting one LHW out of the total 15–20 LHWs serving a particular UC. The random selection will be carried out by an independent researcher not involved in the trial using a simple random table. If the required number of dyads is not completed from one LHW catchment area, we will include the catchment areas of adjacent LHW to reach the required sample size from each UC. This patch of contiguous area/catchment areas of LHWs within that UC will serve as the impact evaluation zone for our trial related outcomes.

### Randomisation

As it is a cRCT, unit of randomisation is cluster. Each cluster is the smallest administrative unit, called UC. Thirty UC clusters will be randomised to the intervention and control arms on a 1:1 allocation ratio using a permuted-block randomisation method. SAS PROC PLAN is carried out to generate a randomisation list by an independent statistician based at University of Liverpool. Allocation of clusters will be carried out by an independent person not involved in the conduct of the trial.

### Informed consent

The trained research team along with LHW will approach the families within the evaluation zones of the UCs to seek informed consent for participation in the trial. For the families who consent for participation in the trial, the research team will evaluate caregiver-child dyad against trial inclusion and exclusion criteria. Baseline assessments will be completed for consenting parent-child dyads. LHW will inform the families about the allocation status. Families randomised to intervention arm will be organised into networks with one champion family volunteer for 5–7 families. A record of outcome of screening, assessment against eligibility criteria, and reasons for refusal will be maintained for those who do not consent for participation in the trial. At the endpoint, researcher will verbally reaffirm the consent.

### Sample and power calculations

The effect size estimates for the primary outcome measure (WHODAS-Child) are informed by the results of the pre-post feasibility study in Pakistan (Hamdani *et al*. 2015) and are in line with the effect sizes reported in a recent WHO supported systematic review of literature for non-specialist delivered psychosocial interventions for developmental disorders in lower middle income countries (Reichow *et al*. 2013).

We aim for a conservative effect size estimate of 0.35 for the primary and secondary outcome measures in the definitive cluster randomised trial.

We propose to recruit a sample of 540 parent-child dyads in 30 clusters (on average 18 parent-child dyad per cluster), equally distributed among the intervention and control arms. This will give 93% power at 5% two sided significance level with an ICC of 0.01 and will account for 15% attrition rate.

Since the study addresses developmental disorders and delays, which are manifested in multiple ways, we expect the clusters to be heterogeneous with respect to diagnosis, severity, age and co-morbid conditions, hence we have chosen a lower value of ICC of 0.01.

### Outcomes evaluation

Baseline and end point assessments (6 months post intervention) on the sample of 540 parent-child dyads will be conducted by the trained research assessment team blind to the allocation status of the trial participants. Research assessment team is trained in administration of all outcome assessment tools, interviewing techniques, and principles of good clinical practices. The assessments will be completed at a venue of participant's choice-either at their own house, or the LHWs house called the ‘Health House’ or at any other household within the community.

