### Primary intervention effectiveness outcome

#### World Health Organization Disability Assessment Schedule Child Version (WHODAS- Child 2.0)

The WHODAS is a 36-item questionnaire measuring functioning and disability. The items represent cognition, mobility, self-care, getting along with others, life activities, and participation in the society. The interviewer administered proxy version (caregiver report) will be used as it is expected children in this population would not be able to self-report. The tool has been translated, culturally adapted and validated for children with developmental disorders in Pakistan and indicted satisfactory psychometric properties in terms of internal consistency, construct validity and factor structure (*Hamdani et al. forthcoming*).

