### Masking

Given the nature of WHO PST programme intervention, it is not possible to mask the participants and facilitators, as well as the qualitative research team staffs. All researchers conducting pre-post quantitative outcome assessments will be masked in the trial. The order of outcome measures ensures that the primary outcome measure (WHODAS) is administered first as this will minimise the risk of bias that can happen if masking is compromised. If unmasking does occur this will be documented, the assessment halted, and a new researcher assigned to complete assessments with that participant.

The trial statistician will also be blinded regarding the treatment code when he develops the statistical analysis plan and writes the statistical programmes, which will be validated and completed using dummy randomisation codes. The actual allocation will only be provided to the study team after lock of the database.

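### Blinded endpoint assessments may be held in the house of the LHW who announces allocation, with nothing requiring her absence or silence, and the masking safeguards do not fully cover disclosure before WHODAS begins

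*Protocol article*

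**What the plan says.** **Venue.** Under Outcomes evaluation, baseline and endpoint assessments are to be "conducted by the trained research assessment team blind to the allocation status of the trial participants". The same paragraph fixes where they happen: "The assessments will be completed at a venue of participant's choice", which may be "either at their own house, or the LHWs house called the ‘Health House’ or at any other household within the community".

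**Who knows the arm.** Under Informed consent, after the baseline assessments: "LHW will inform the families about the allocation status". Under Enhanced treatment as usual, "LHWs in the ETAU arm will receive training in recognising signs and symptoms of developmental disorders and delays", so in control UCs she is also part of the arm's care.

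**Primary outcome.** WHODAS-Child is answered by the caregiver: "The interviewer administered proxy version (caregiver report) will be used". The Masking section accepts that participants cannot be masked.

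**Safeguards.** The Masking section gives two. The first is order: "The order of outcome measures ensures that the primary outcome measure (WHODAS) is administered first". The second is a response rule: "If unmasking does occur this will be documented, the assessment halted, and a new researcher assigned to complete assessments with that participant".

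**Unit of allocation.** The UC is randomised (Randomisation), with 30 UCs and on average 18 dyads in each (Sample and power calculations). The evaluation zone in a UC starts from one randomly selected LHW's catchment and takes in adjacent ones only if numbers fall short (Procedure to identify eligible participants).

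**The concern.** The primary outcome is a caregiver interview, and the caregiver knows the arm. The assessor's masking is therefore the only masking left when WHODAS is collected. The venue list works against it, because it lets the interview take place in the home of someone who knows the arm and has already discussed it with the families. If she mentions it when the assessor arrives, the interviewer knows the arm before the first item and may prompt or score differently.

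Clustering widens the consequence. All dyads in a UC share an arm, and many or all may share one LHW, so a remark about one family informs the assessor about the rest.

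A smaller, related gap is the third venue option, a different household. It does not involve the LHW, but nothing stops it being the home of a champion volunteer, who delivers the programme and exists only in intervention UCs.

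**Working it through.** **1. Order of events against the safeguards**

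| When the arm is disclosed | WHODAS-first | Halt-and-replace |
|---|---|---|
| On arrival, before the first item | No protection | Applies if noticed, for that participant only |
| During WHODAS | Protects only the items already asked | Applies if noticed, for that participant only |
| After WHODAS | Protects this dyad's primary outcome | Applies if noticed, for that participant only |
| At another dyad's visit in the same UC | No protection for later dyads | Not covered as worded |

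The first and last rows are the gap. A replacement assessor could also be sent to the same venue.

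**2. Reach of one disclosure within a UC**

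Input: 18 dyads per UC, one arm per UC.

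- Other dyads whose arm is revealed: 18 − 1 = 17, or 17/18 = 94%.
- With the planned 15% attrition: 18 × 0.85 = 15.3 dyads seen at endpoint, so about 14 others.

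These are ceilings. They are reached only if the disclosure comes at the first endpoint visit in that UC and the same assessor sees every remaining dyad. The article states neither.

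**3. How often the LHW's house might be used**

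The article gives no uptake. Assume 10% to 30% of families choose it, independently.

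- Expected visits per UC: 18 × 0.10 = 1.8 to 18 × 0.30 = 5.4.
- Chance that a UC has no such visit: 0.9^18 = 15% at the low end, 0.7^18 = 0.2% at the high end.
- UCs with no such visit: 30 × 0.15 = 4.5 at the low end, and close to none at the high end.

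These count visits, which are opportunities for disclosure. They do not count unmaskings.

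**4. What bias could do to the test (illustration only)**

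First, the plan's own figure. Inputs from Sample and power calculations: 270 dyads per arm, 15% attrition, ICC 0.01, effect 0.35 SD, two-sided 5%.

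- Analysed per arm: 270 × 0.85 = 229.5.
- Design effect: 1 + (15.3 − 1) × 0.01 = 1.143.
- Effective number per arm: 229.5 / 1.143 = 200.8.
- Standard error: √(2 / 200.8) = 0.0998 SD.
- Power: Φ(0.35 / 0.0998 − 1.96) = Φ(1.547) = 93.9%, which agrees with the stated 93%.

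Now assume a fraction f of endpoint assessments is unmasked before WHODAS and each shifts the arm contrast by b SD in one direction. The bias is f × b, and the two-sided type I error is Φ(−1.96 − bias/SE) + 1 − Φ(1.96 − bias/SE).

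| f | b (SD) | Bias (SD) | Type I error |
|---|---|---|---|
| 0.10 | 0.1 | 0.010 | 5.1% |
| 0.25 | 0.2 | 0.050 | 7.9% |
| 0.50 | 0.3 | 0.150 | 32% |

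Neither f nor b is in the article. The table shows only that the result runs from negligible to serious depending on values nobody has stated.

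**The case against.** **Presence and disclosure are inferred.** A reader might take the text to put the assessor together with the LHW. It does not. It allows her house as one of three venues at the participant's choice, and nowhere says that she attends or speaks of the arm. This stands. What remains is that it is her home and nothing requires her to be away or silent.

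**LHWs serve both arms.** Meeting one reveals nothing unless she speaks, and her control-arm training is not visible. This stands, so her mere presence should not be called different by arm.

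**The plan has a second safeguard.** Halt-and-replace is not limited to disclosure after WHODAS, so a noticed disclosure on arrival triggers it. This stands in part. It would be wrong to say that the safeguards fail at this venue: WHODAS-first still covers later disclosure, and the rule handles recognised unmasking of that participant. It leaves unnoticed unmasking and the other dyads in the UC.

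**The caregiver can disclose anywhere.** She is unmasked at her own home too. True, and no venue rule removes it. That risk is unavoidable, whereas the use of the LHW's house is not.

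**This is a condensed article.** Instructions on who may attend could sit in the full protocol. They may. But the article itself fixes the venue list, and that list pulls against its own masking requirement.

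**Conclusion.** The point holds as an avoidable risk to assessor masking, not as evidence that masking will fail. The article permits blinded endpoint interviews in the home of the person who announces allocation, without requiring her absence or silence. WHODAS-first does not address disclosure on arrival, and halt-and-replace depends on recognition and stops at the single participant although the arm belongs to the whole UC.

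The size cannot be fixed from the document. Up to 17 further dyads per affected UC is an upper limit under the conditions set out above. Two stronger readings are unsupported. One is that 94% of a cluster would be unmasked, which treats a visit as a disclosure. The other is that nearly every UC would have a visit to the LHW's house: at 10% uptake about 15% of UCs would have none. The power calculation is unaffected. I rate this a minor to moderate point, worth acting on because the primary outcome depends on an interviewer and the change is cheap.

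**What to change.** 1. In Outcomes evaluation, for endpoint assessments in both arms, remove the LHW's house from the venue list and use the family's own home or another household. If it must stay, require at minimum that the LHW is absent during the visit and does not disclose allocation to the assessor.
2. Where a family offers another household, have unmasked field staff check that it is not the home of another family's champion volunteer. The assessors must not hold such a list: it would exist only in intervention UCs and would itself reveal the arm. A volunteer who is herself an enrolled caregiver can still be seen at home.
3. In Masking, record for each unmasking whether it came before, during or after WHODAS. The sponsor could also consider reassigning that assessor's remaining visits in the same UC, since the present rule covers one participant only.

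The cost is a few sentences of wording and a short field instruction. Some families lose a convenient venue and assessors travel a little more. Item 2 needs a small amount of unmasked staff time, and the optional reassignment in item 3 needs a second masked assessor available for that UC.
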